## Abstract

**Background:**

Hypertension contributes to a significant burden of cardiovascular disease in low- and middle-income countries; however, responses are inadequate because of a lack of conclusive evidence on population-based approaches to hypertension control.

**Methods/design:**

The objective of the present study is to determine the effect of family-based home health education and blood pressure monitoring by trained female community health volunteers. The primary outcome is change in mean systolic blood pressure. A community-based, open-masked, two-armed, cluster-randomized trial will be conducted in Lekhnath Municipality of Nepal. The municipality is divided into 15 administrative clusters. Randomization will be conducted for 14 clusters: 7 for the intervention arm and 7 for the control arm. The participants were recruited from a prevalence study conducted earlier. On the basis of population proportion size, 929 individuals for the intervention group and 709 individuals for the control group will participate in the study. Due to the nature of the study, study participants are not compensated or insured. As part of the blood pressure intervention, trained female community health volunteers will conduct home visits for health education and blood pressure measurement. The primary outcomes will be modeled by using multiple linear regression analysis.

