### Sample size calculation 

The sample size for the population prevalence study is estimated according to the method suggested in the WHO STEPwise approach [23]. We calculated the sample size for 95 % CI (*z* = 1.96) on the basis of a 5 % margin of error (α), a 25 % estimated prevalence of hypertension based on the latest nationwide study in Nepal [25], a design effect of 1, and a response rate of 80 %. We will include only an age group ≥ 25 years old, resulting in a total of four age groups for each sex (total strata = 8). This will result in a sample size equal to 2882. The participants in the baseline survey will be eligible to participate in the intervention study. For the intervention study, we took the reference of the mean difference and SD from studies conducted in Vietnam and Taiwan [26, 27]. As our project is randomized and includes visits by community health workers who measure blood pressure for screening additionally, we are hopeful that we will observe a 5-mmHg difference in mean SBP between the control and intervention arms. The detailed assumptions of the sample size calculation are presented in Table 2.

**Table 2 Tab2:** Sample size calculation

Category	Mean difference (mmHg)	SD	Intracluster correlation coefficient	Design effect	Clusters per arm	Individuals per arm	Total sample size
Normotensive	5	18.8	0.01	1.57	7	406	812
Prehypertensive	5	13.6	0.01	1.23	7	168	336
Hypertensive	5	15.7	0.01	1.34	7	245	490

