### Data analysis

The quantitative analysis will be done using STATA version 14 software (StataCorp, College Station, TX, USA) following the Consolidated Standards of Reporting Trials (CONSORT) guidelines for cluster-randomized trials. Flowcharts (Fig. 1) will include the number of participants seen at each stage of the trial, including the number screened, eligible, randomized, and analyzed for the primary outcome. In initial analysis, we will compare baseline characteristics of enrolled participants in the study intervention arm and follow-up status. The primary analyses will be intention to treat at the 12-month follow-up, adjusted for the baseline measure of the outcome. In the event that randomization does not control for differences between the treatment and control groups on baseline characteristics, we will statistically control for those differences in subsequent analyses of program effects. The final outcome will be modeled by using random - effects regression models. The effect size will be reported as mean differences with 95 % CIs for primary data.

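### The abstract and the Data analysis section name different models for the primary outcome, and only the random-effects model fits the randomisation of 14 wards

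*Protocol article*

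**What the plan says.** The protocol article describes the model for the primary outcome twice.

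- Abstract, Methods/design: "The primary outcomes will be modeled by using multiple linear regression analysis". Clustering is not mentioned in connection with the model.
- Data analysis: "The final outcome will be modeled by using random - effects regression models". The same section commits to CONSORT for cluster-randomised trials, intention to treat at 12 months, adjustment for baseline, and mean differences with 95% confidence intervals.

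The design is clustered throughout. The abstract says "Randomization will be conducted for 14 clusters: 7 for the intervention arm and 7 for the control arm", and gives the sample as "929 individuals for the intervention group and 709 individuals for the control group will participate in the study". Table 2 (Sample size calculation) sizes each blood pressure category separately, with an ICC of 0.01 and 7 clusters per arm. Its rows read "Normotensive 5 18.8 0.01 1.57 7 406 812", "Prehypertensive 5 13.6 0.01 1.23 7 168 336" and "Hypertensive 5 15.7 0.01 1.34 7 245 490". The columns are mean difference, SD, ICC, design effect, clusters per arm, individuals per arm and total.

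**The concern.** Multiple linear regression, in its usual meaning, treats every participant as an independent observation. Here the ward is the unit of randomisation, and the sample was enlarged to pay for correlation within wards. A regression that ignores wards would give standard errors that are too small, confidence intervals that are too narrow and a type I error above the nominal level, on the primary outcome.

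The article also leaves two models on record for that outcome, and either could later be cited as the planned one. A published protocol should leave only one.

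**Working it through.** **Inputs.** From Table 2: ICC 0.01, 7 clusters per arm, and 406, 168 and 245 individuals per arm. From the abstract: 929 and 709 participants, 1,638 in total, and 14 wards. Two-sided 5% is inferred from the 95% confidence intervals in Data analysis; no alpha is stated for the trial comparison. Power is not stated either; 80% is assumed below, only to reproduce Table 2.

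**Step 1: reproduce Table 2.** The design effect is DE = 1 + (m − 1) × ICC, with m the individuals per arm divided by 7.

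- Normotensive: m = 406/7 = 58; DE = 1 + 57 × 0.01 = 1.57
- Prehypertensive: m = 168/7 = 24; DE = 1 + 23 × 0.01 = 1.23
- Hypertensive: m = 245/7 = 35; DE = 1 + 34 × 0.01 = 1.34

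All three match. The sample sizes follow too. Take n0 = 2 × [SD × (2.179 + 0.842)/5]², where 2.179 is the two-sided 5% t value on 12 degrees of freedom and 0.842 is the normal quantile for 80% power. Then m = n0 × 0.99/(7 − 0.01 × n0), rounded up, times 7.

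- SD 18.8: n0 = 257.96, m = 57.8, rounded up to 58, giving 406
- SD 13.6: n0 = 134.99, m = 23.7, rounded up to 24, giving 168
- SD 15.7: n0 = 179.90, m = 34.2, rounded up to 35, giving 245

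So the sizing accounts for clustering, and its figures agree exactly with a test on 12 degrees of freedom (14 wards less 2 arms).

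**Step 2: type I error if wards are ignored.** The unclustered standard error is too small by a factor 1/√DE, so the true two-sided error of a nominal 5% test is 2 × Φ(−1.96/√DE).

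| Analysis | DE | SE understated by | 1.96/√DE | Type I error |
|---|---|---|---|---|
| Prehypertensive | 1.23 | 10% | 1.767 | 7.7% |
| Hypertensive | 1.34 | 14% | 1.693 | 9.0% |
| Normotensive | 1.57 | 20% | 1.564 | 11.8% |
| Pooled, 1,638/14 = 117 per ward | 1 + 116 × 0.01 = 2.16 | 32% | 1.334 | 18.2% |

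**Step 3: checks on the pooled figure.** With the stated split, the ward averages are 929/7 = 132.7 and 709/7 = 101.3. The variance ratio is (2.317/929 + 2.003/709)/(1/929 + 1/709) = 2.14, which gives 18.0%. A simulation of 20,000 trials at these sizes and ICC 0.01 gave 17.8% for the unclustered comparison and 5.0% for a t-test on ward means.

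**Step 4: sensitivity, using assumed values that are not in the article.** Unequal ward sizes raise the pooled rate to 18.5%, 19.8% and 22.0% at coefficients of variation of 0.2, 0.4 and 0.6. With equal ward sizes, the pooled rate is 11.9% at ICC 0.005, 28.2% at 0.02 and 45.2% at 0.05.

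**The case against.** The strongest reply is that the Data analysis section governs. It is the detailed text, it already names random-effects regression, and it invokes the reporting standard for cluster trials. On that view the abstract contains a loose summary sentence and nothing in the analysis has to change. This largely stands. It limits the seriousness of the point, but it does not remove the conflict, because no text says which statement prevails.

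A second reply is that the abstract's wording need not mean independent errors. A linear mixed model with covariates is sometimes loosely called multiple linear regression, and a linear regression can carry cluster-robust standard errors. The same abstract calls the trial cluster-randomised. This also stands, so the inflation figures are conditional on an unclustered analysis.

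Third, a reader might infer that the plan carries an 18% false-positive rate. The article does not support that. The figure needs an unclustered fit, one pooled comparison of all 1,638 people and an ICC of 0.01. The Primary and secondary outcomes section names the three blood pressure populations, and Table 2 sizes them separately, which points to analysis by category and to about 8% to 12%. The ICC is also a planning value, and the correlation that remains after baseline adjustment may differ from it.

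Finally, a reader might infer that the model is to be chosen after both results are seen. The ambiguity would permit that, but nothing in the article suggests it is intended.

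**Conclusion.** The contradiction is real: two models are named for the primary outcome, and only random-effects regression matches the randomised unit and the sample-size basis. The consequence is conditional. If the abstract's model were run without allowance for wards, the type I error at ICC 0.01 would be about 8% to 12% by blood pressure category and about 18% for a single pooled comparison. These figures assume a two-sided 5% test, equal ward sizes and an ICC that baseline adjustment leaves at 0.01. If the Data analysis section is followed, none of this inflation arises and the planned analysis stays as it is. The point is a necessary correction of wording on a primary-outcome item; it does not show that the trial plans an invalid test.

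**What to change.** Correct the abstract sentence to agree with the Data analysis section, and state the same primary model in both places: 12-month SBP regressed on arm and baseline SBP, with a random intercept for ward and a small-sample degrees-of-freedom correction such as Kenward-Roger or Satterthwaite. The correction belongs in the statement because, with 14 clusters, a random intercept tested against normal critical values does not by itself secure the nominal 5%.

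The cost is a sentence or two of text. Confidence intervals will be somewhat wider than an unclustered or uncorrected analysis would give. On 12 degrees of freedom the correction alone widens them by about 11% (2.179/1.960 = 1.11). Table 2 reproduces with that same t value at an assumed 80% power, so on that assumption the sample size already covers this.

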**Discussion:**

This project will be an investigation of a community-based intervention to control blood pressure in countries with limited resources. The study will provide detailed information on the burden of blood pressure and also whether treatment targets are being met. Moreover, evidence will be provided on the future role of female community health volunteers for hypertension management in Nepal. The lessons learned from this study may also be replicated in other rural areas of Nepal and elsewhere in the world with similar settings.

**Trial registration:**

ClinicalTrials.gov NCT02428075. Registered on 23 April 2015.

**Electronic supplementary material:**

The online version of this article (doi:10.1186/s13063-016-1412-3) contains supplementary material, which is available to authorized users.

## Background

The burden of hypertension worldwide contributes significantly to heart failure, coronary artery events, stroke, kidney failure, disability, and premature death [1]. Modifiable lifestyle behaviors such as tobacco use, physical inactivity, unhealthy diet, and alcohol abuse are the major risk factors contributing to the rising incidence of high blood pressure [2]. A population-based approach to decreasing blood pressure levels in the general population by even modest levels has the potential to substantially reduce morbidity and mortality and possibly to delay the onset of hypertension [3]. It has been estimated that a 5-mmHg reduction of systolic blood pressure (SBP) in the population would result in a 14 % overall reduction in mortality due to stroke, a 9 % reduction in mortality due to coronary heart disease, and a 7 % decrease in all-cause mortality [3, 4]. A study published in 1998 showed that the association between blood pressure and stroke in East Asia seems higher than in Western populations. A population-wide reduction of 3 mmHg in diastolic blood pressure is predicted to eventually decrease the number of strokes by about one-third [5].

**Fig. 1 Fig1:**
[figure not shown]
Planned flow of participants through the trial. *FCHV* female community health volunteer

However, community-based protocols to reduce blood pressure via lifestyle interventions remain poorly defined. Two studies on health promotion for blood pressure reduction have yielded inconclusive results [6, 7]. We have identified deficiencies in study design in a number of previous studies, such as contamination bias. For example, there has been a lack of detail about health workers, and many were demonstration projects without a concomitant control group [8–13]. Reduction of dietary salt in Sub-Saharan Africa lowered blood pressure in the short term [14], and a study conducted in Pakistan showed small but significant differences in blood pressure among children and young adults in the intervention group compared with the control group [15]. However, there is still a lack of evidence on effective protocols for community health worker population approaches to reducing blood pressure in normotensive, prehypertensive, and hypertensive groups. Indeed, we noted in our previous meta-analysis that there is a variable prevalence of hypertension across South Asian Association for Regional Cooperation countries, with people in a number of countries having blood pressure above the global average. In Nepal, the prevalence of hypertension ranges from 22 % to 34 % [16]. We also noted that studies are not consistent in their data collection methods regarding hypertension and related modifiable risk factors [16]. Hence, a benefit of the present study will be to provide an accurate prevalence rate and risk factors for hypertension, and also to design an intervention for hypertension management at the community level.

One of the possibilities for addressing emerging hypertension in low- and middle-income countries could be by involving community health workers, such as female community health volunteers (FCHVs) in the setting of Nepal [17]. In Nepal, there are over 50,000 FCHVs working to improve the health of their communities [18], and they are highly recognized for the contribution they have made to improving maternal and child health [19]. Nepal’s Ministry of Health and Population relies on FCHVs to act as health resources in their villages by educating their neighbors about important health issues and providing basic health services in the absence of other biomedical resources.

FCHVs are selected by members of Mothers’ Group for Health with the help of local health facility staff. They receive 18 days of basic training in two phases (9 + 9 days) on selected primary health care components. The current role of the FCHV is to promote health and healthy behaviors of community-dwelling people to promote safe motherhood, child health, and family planning [18]. According to the National Female Community Health Volunteer Survey, the median age of FCHVs is 37 years, and 42 % have completed primary school education or higher [20]. Despite FCHVs’ positive record of collaborating with the official health system, these cadres have yet to be mobilized for prevention, control, and treatment of hypertension. The initial service to be promoted in the present trial design is for the FCHV to be skilled in monitoring blood pressure, providing health promotion counseling, and referring at-risk patients to the nearest health center for hypertension treatment. In our earlier feasibility study, FCHVs expressed willingness and readiness to be trained in hypertension management [21]. The FCHVs serve as a unique link between the health facilities and local communities, and they have the potential to play an important role in promoting knowledge and awareness of healthier lifestyles and thereby reducing the risk of hypertension. Thus, the aim of this study protocol is to determine the effect of family-based home health education and screening of blood pressure in adults by FCHVs in Nepal.

## Methods/design

### Study design and setting

A community-based, open-masked, two-armed, cluster-randomized trial will be conducted in Lekhnath Municipality of Nepal. The municipality is located in the western region of Nepal, about 180 km west of Kathmandu. The total population of the municipality was 58,816 in the census carried out in 2011. The municipality is divided into 15 smaller units called *wards*. The municipality is a semiurban area with limited health services comprising one primary health care center, three sub-health posts, and two urban health care centers. According to information provided by District Public Health Office, Kaski in 2013, there were 123 FCHVs in the municipality. No community-based interventions for hypertension at the population level have been carried out in this region to date.

### Recruitment

A population framework of all eligible participants will be prepared from the voter list prepared by the Election Commission in 2007. As of 15 December 2006, all the people included in the voter list were at least 18 years old. By 2015, all the people in the voter list were at least 25 years of age. The voter list also contains information about the household. Using the voter list, a survey will be carried out by trained health professionals such as nurses and health assistants to estimate the proportion of hypertension in the municipality as well as to prepare a list of eligible respondents to participate in our randomized controlled trial. The data enumerators will receive 5 days of intensive training before collecting data.

If there is more than one participant from the same household eligible to participate in the study at the time of data collection, the Kish method will be adopted to select the participant [22]. The survey tool will be adapted from the World Health Organization (WHO) STEPwise approach to surveillance [23], which includes physical measurement (height, weight), sociodemographic information (e.g., age, sex, family size, occupation, income, education), lifestyle factors (e.g., salt consumption, smoking, alcohol, physical activity), and blood pressure measurement. The classification of normotension, prehypertension, and hypertension is shown in Table 1.

**Table 1 Tab1:** Classification of normotension, prehypertension, and hypertension

SBP/DBP level, mmHg	Taking antihypertensive medication	Status for recruitment
< 120/80		
Yes	No	Normotensive
No	Yes	Hypertensive
≥ 120/80 and < 140/90		
Yes	No	Prehypertensive
No	Yes	Hypertensive
≥ 140/90		
Yes	No	Hypertensive
No	Yes	Hypertensive

*DBP* diastolic blood pressure, *SBP* systolic blood pressure

During that survey, normotensive, prehypertensive, and hypertensive participants will be identified and asked to participate in the study. From among eligible participants, the required sample size of respondents will be chosen in proportion to the population of the specific ward to be sampled. On the fifth day of training, FCHVs from one cluster will sit together and allocate the number of households that has to be visited on the basis of the baseline survey. After that, FCHVs will visit each household, meet the selected participant, and ask for consent to participate in the trial.

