### Randomization

Of 15 wards (clusters), 1 ward will be excluded by lottery method before randomization. Clusters will be randomly assigned to intervention and control areas using a 1:1 allocation ratio. Randomization will be done before the participants are recruited. Research teams responsible for identifying potential participants, obtaining consent, and recruiting trial participants will be blinded to the participants’ allocation status. The following steps will be taken to avoid selection bias during random allocation: (1) clusters will be randomized only after the baseline survey; (2) clusters will not be withdrawn from or added to the study; and (3) an epidemiologist who does not come in contact with the study will randomize the clusters.

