### Intervention

After randomization, the FCHVs participating in the intervention wards will receive a 5-day training package featuring (1) introduction and importance of noncommunicable disease and/or hypertension; (2) identifying populations at risk using a checklist comprising level of salt intake, physical inactivity, smoking, and alcohol consumption; (3) blood pressure screening by using digital sphygmomanometers, height and weight measurement, and referral for those whose blood pressure is > 140/90 mmHg; (4) providing health education in major risk factors; and (5) recording, reporting, and follow-up. Educational sessions are guided by use of the Health Belief Model [28], and training materials will be developed by involving local major stakeholders. The developed materials will be pretested with the FCHVs of Pokhara Municipality.

After receiving the training, the FCHVs will be given a digital sphygmomanometer, manual weighing scale, clinical measuring tape for height, an FCHV manual, and a recording register. During the training program, FCHVs will allocate the households themselves. On average, 1 FCHV will visit 25 households (13 normotensive, 5 prehypertensive, and 7 hypertensive). Each FCHV will visit selected households three times during 1 year, where the FCHV will provide counseling and measure the blood pressure as well as the height and weight of selected respondents. If the participant is hypertensive, the FCHV will ask the respondent to visit the health facility for further diagnosis and treatment. For hypertensive participants, the FCHV will also monitor whether the respondent is taking medicine as per the advice of health care workers. Participants in the control clusters will receive usual care. Usual care means current practices related to hypertension management at the community level. After the 1-year period of the intervention, a follow-up survey will be carried out through trained professional health workers such as nurses and health assistants.

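### Recruiters are said to be blinded, yet in the intervention wards consent is sought after allocation by the volunteers trained to deliver the intervention

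*Protocol article*

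**What the plan says.** The protocol article treats consent in three places.

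- **Randomization** fixes the order and claims blinding: "Randomization will be done before the participants are recruited". Then: "Research teams responsible for identifying potential participants, obtaining consent, and recruiting trial participants will be blinded to the participants’ allocation status". It also says that wards are allocated only once the baseline survey is complete.
- **Recruitment** describes the consent step: "On the fifth day of training, FCHVs from one cluster will sit together and allocate the number of households". Directly after this: "FCHVs will visit each household, meet the selected participant, and ask for consent to participate in the trial". The same section says that survey respondents are identified and invited to take part during the survey itself.
- **Intervention** dates the training and names its audience: "After randomization, the FCHVs participating in the intervention wards will receive a 5-day training package". It adds: "During the training program, FCHVs will allocate the households themselves". The same volunteers then deliver the intervention: "Each FCHV will visit selected households three times during 1 year, where the FCHV will provide counseling and measure the blood pressure".

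The section on inclusion and exclusion criteria removes people who decline consent. Control wards receive usual care, and the article does not say who asks for consent there.

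**The concern.** When clusters are randomised before individuals consent, concealing the allocation from recruiters is the main protection against selection at the individual level. The three numbered steps under Randomization (allocation after the survey, no change of clusters, an independent randomiser) protect the allocation of wards. They do not protect what happens when a person is later asked to join.

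A volunteer who has just been trained to give the counselling knows her ward's arm, and may encourage some people more than others. The intervention is education and behaviour change, so willingness to accept her visits could plausibly predict how SBP changes over the year. If refusal follows a different pattern in the two arms, the groups compared are no longer those that randomisation produced. The Data analysis section adjusts for the baseline value of the outcome. That handles differences in measured SBP, but not differences in motivation.

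**Working it through.** **Order of events, from the article's own statements**

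1. Nurses and health assistants carry out the survey and prepare the list of eligible people (Recruitment).
2. Wards are allocated after the survey (Randomization).
3. FCHVs of intervention wards take a five-day course after allocation and divide the households among themselves during it (Intervention).
4. On day five the FCHVs of a ward divide the households, then visit them and ask for consent (Recruitment).
5. The FCHVs make three counselling and measurement visits (Intervention).

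**Are steps 3 and 4 the same course?** The length matches, the household-sharing task matches, and the article describes no other FCHV training. In the intervention wards, then, consent comes after allocation and is sought by people who know it.

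**Can another reading remove the conflict?**

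- *Consent was really given during the survey.* Then the statement that randomisation precedes recruitment is wrong, and the later FCHV consent visit has no purpose.
- *The research teams do not include FCHVs.* Then one section gives consent-taking to the research teams and another gives it to the FCHVs.
- *The trial is declared open.* That label covers the trial in general. The Randomization section makes a specific claim about recruiters.

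Under each reading at least one sentence must change.

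**Size.** The article gives no consent or refusal rates, so no bias can be estimated. Its form can be written down. In one arm let *p* be the share of selected people who decline, R the mean SBP change of those who join, and N that of those who decline, both after baseline adjustment.

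- Mean of all selected = (1 − p)R + pN.
- Mean of those who join minus mean of all selected = p(R − N) = pD, where D = R − N.
- Bias in the between-arm difference = p_I·D_I − p_C·D_C (I intervention, C control).

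This is zero if nobody declines, if declining is unrelated to SBP change, or if the pattern is the same in both arms.

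As pure assumptions, take p from 5% to 20% in one arm, D from 0 to 10 mmHg in absolute value, and no such loss in the other arm. The bias then runs from 0 to 0.20 × 10 = 2 mmHg. The top of that range needs a D of twice the whole 5-mmHg target effect. A bias of 1 mmHg (1/5 = 20% of the target) would need, for example, 20% × 5 mmHg or 10% × 10 mmHg.

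For scale, Table 2 can be reproduced. The design effects are 1 + (406/7 − 1) × 0.01 = 1.57, 1 + (168/7 − 1) × 0.01 = 1.23 and 1 + (245/7 − 1) × 0.01 = 1.34, as printed. The standard error of a difference is SD × √(2 × design effect / n per arm):

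- Normotensive: 18.8 × √(2 × 1.57/406) = 1.65 mmHg
- Prehypertensive: 13.6 × √(2 × 1.23/168) = 1.65 mmHg
- Hypertensive: 15.7 × √(2 × 1.34/245) = 1.64 mmHg

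A 1-mmHg bias would be 1/1.65 ≈ 0.6 of a standard error. This shows what would have to be true for the bias to matter. It is not an estimate.

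**The case against.** The strongest reply is that most of the selection is settled before allocation. The eligible list and baseline SBP come from survey staff. FCHVs meet people already selected and cannot bring in motivated people from outside the list. Respondents had also been invited during the survey, which may leave little refusal for later. The independent randomiser and the fixed set of wards are not in question. All of this stands, and it narrows the exposure to the consent or refusal step. It does not make the blinding statement true. Condensing a protocol into an article excuses missing detail, but not two statements that cannot both hold.

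A reader might infer four stronger claims that the article does not support:

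- *Severe illness and expected absence were judged after allocation, by different people in each arm.* The article does not say who applies these exclusions or when, and the survey's task of listing eligible people points to an earlier stage.
- *Consent was handled differently in control wards.* The control route is undescribed, which is not evidence that it differed.
- *The planned 929 versus 709 participants show unequal consent.* The abstract attributes the split to population size, and 929 + 709 = 1638 equals the Table 2 total (812 + 336 + 490).
- *Comparability has been lost.* Nothing shows that differential recruitment occurred.

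**Conclusion.** The contradiction is certain on the text. In the intervention wards the people who ask for consent cannot be blinded, so the trial cannot claim blinded recruitment as the article describes it. This rests on one inference, that the training in the Recruitment section is the course in the Intervention section, and both sections' details support it. Differential consent or refusal is a plausible risk and not a demonstrated fact. Its size cannot be derived from the article, and the importance of the point does not depend on the illustrative range. The point matters because the sentence is offered as protection for the primary comparison, and baseline adjustment is only a partial substitute.

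**What to change.** Accrual has closed according to the Trial status section, so consent cannot be moved ahead of allocation. What can be done:

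1. Reconcile the Recruitment, Randomization and Intervention sections. State for each arm who obtained trial consent, when this was relative to randomisation, whether those people knew the allocation, and what the invitation during the survey amounted to.
2. If consent followed allocation, withdraw the claim of blinded recruitment.
3. In that case, report the numbers selected, approached, excluded and consenting by ward and arm, with the survey's baseline SBP, age and sex for people who did not take part. The planned CONSORT flowchart covers part of this. The breakdown at the consent step and the profile of non-participants would be the addition.
4. Add a sensitivity analysis that weights participants by the inverse of their estimated probability of taking part. Estimate that probability from baseline-survey variables, and keep the ward structure in the analysis. Say plainly that it corrects measured differences only. Like baseline adjustment, it cannot reach unmeasured motivation.

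The cost is revised wording, one extra analysis on survey data already held, and a less favourable statement on selection bias in the final report.
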